## Aims

The objective of the study is to evaluate the benefit of early and intensive relapse prevention in the context of MPT. The goal is to prevent the chronification of back pain and thus reduce the high direct and indirect costs. To answer this question, outcome, process and cost-effectiveness evaluations will be performed. The aim of outcome evaluation is to examine the intervention effect on patient-relevant outcomes. Process evaluation will examine the extent to which the intervention has been carried out and how the process is perceived and evaluated from the perspective of service providers and patients. Indirect and direct costs will be considered in the health economic evaluation.

From this, the following hypotheses can be derived:

H_1_: the intervention reduces the days of incapacity to work (outcome evaluation).H_2_: the intervention increases the functional capacity (outcome evaluation).H_3_: the intervention is perceived positively by the participating patients (process evaluation).H_4_: the intervention reduces direct and indirect costs (health economic evaluation).

## Methods and analysis

### Study design

In order to answer the research questions, outcome, process and health economic analyses will be carried out. Different research methods will be used for this purpose. The comparative population will be formed by randomising the groups of participants. The division into the respective groups (intervention group, IG or control group, CG) will be carried out monthly to ensure that the patients of both groups are not able to exchange information with each other. Patients who start an MPT simultaneously in the Rehabilitation Center each form a cluster. These clusters will be randomised to the IG or CG (see figure 2). The evaluator will inform the Rehabilitation Center monthly via email in the third week of the MPT whether the group is an IG or CG. Up to this point, neither the patient nor the treatment staff will know which group the patient belongs to. The recruitment period will be 24 months.

**Figure 2 F2:**
[figure not shown]
Study design. MPT, multimodal pain therapy; RP, relapse prophylaxis.

### Outcome evaluation

The results will be derived from a cluster-randomised controlled trial. The evaluation design incorporates an IG as well as a CG and surveys at three different points in time (see figure 2). Both groups will participate in the MPT programme. While IG members will additionally receive relapse prevention modules, the CG will undergo usual care. The primary outcome represents the number of days of incapacity to work within 1 year after the end of MPT. It is assumed that in the present sample, the average number of 37 days off work per year will decrease in the IG by 40% (or 15 days) compared with the CG. One secondary outcome addresses the functional capacity. It is assumed that the functional capacity in the IG will be significantly (p<0.05) higher than in the CG. In addition, patient and provider satisfaction with the intervention will be explored, including barriers, hurdles and potentials. Direct and indirect costs are another outcome and will be compared between IG and CG.

### Process evaluation

To evaluate the process quality, we will examine the assignment of participants to the standard and the complex programme along with the distribution of the IG to low, medium and high intensity RP. In addition, we will consider usage of the modules (eg, medical training therapy, psychological support and phone consultation) as well as the app utilisation. To examine the quality of the intervention, patients will receive additional questions about their satisfaction with individual MPT and RP modules within the survey. In order to evaluate experiences and satisfaction with the intervention, guided interviews will be conducted. These will be carried out with all physicians, psychologists and physiotherapists involved.

### Health economic analysis

The health economic analysis will examine the costs, cost savings and cost effectiveness of the intervention. Therefore, intervention costs, expenditures of healthcare utilisation, indirect costs due to incapacity to work and the patient’s health-related quality of life will be assessed. For the calculation of indirect costs, the days of incapacity to work are multiplied by the average hourly wage in Germany, taking into account whether the individuals work full time or part time. The evaluation will be carried out based on claims data. Incremental cost effectiveness will be analysed by considering direct and indirect costs as well as the health-related quality of life of both groups, IG and CG.

### Measurements

Various instruments will be used in the course of primary data collection, including standardised questionnaires (table 1). Prior to the start of MPT, the IG and CG will receive a questionnaire to assess the status quo at the beginning of the intervention (T0). The questionnaire will be handed out directly at the Rehabilitation Center or sent by mail in individual cases for T0 and after the 4-week MPT programme (T1). It will comprise various items on socio-demographic and socioeconomic parameters together with health-related behaviour (exercise, diet, smoking, etc). Health-related questionnaires will be the Heaviness of Smoking Index,^22^ the AUDIT alcohol consumption questionnaire, an effective brief screening test for problem drinking^23^ and the Pain Disability Index.^24^ In addition, the questionnaire will include items about how often and to what extent the study participants exercise,^25^ as well as questions about diet and nutrition.^26^ In addition, standardised survey instruments will be included to assess functional capacity (Questionnaire for the diagnosis of functional disability caused by backache, FFbH-R)^27^ and health-related quality of life (EQ-5D).^28^ A Visual Analogue Scale will be used to assess the patient’s health-related quality of life from 0 to 100. IG and CG will receive further questionnaires 12 months post intervention (T2). All questionnaires except for T0 will include questions regarding patient satisfaction and experience with the intervention. Two weeks after handing out or sending the questionnaire, patients who have not yet responded will receive a reminder to increase the response rate. A second reminder will be sent after an additional 10 days. Reminders and the final questionnaires (T2) for the IG will be sent by the Rehabilitation Center, while those for the CG will be sent by the health insurance fund.

**Table 1 T1:** Quantitative and qualitative data sources

Target group	Data source	Data type	Instrument	Parameter
Patients	Primary data	Quantitative	Questionnaire	Age, gender, sociodemography, satisfaction, functional capacity, health-related quality of life, impairment due to pain, health behaviour, sports activity, nutrition, smoking and alcohol
Medical staff and psychologists	Primary data	Qualitative	Interview	Motivation, expectations, experiences, hurdles and barriers, suggestions for improvement and satisfaction with the intervention
Patients	Secondary data	Quantitative	Claims data	Days of incapacity to work, region, pharmaceuticals, therapeutic products and outpatient and inpatient care

Secondary data will be included in the analyses based on claims data of the regional health insurance fund AOK Lower Saxony. These will include inpatient treatment, rehabilitation services, pharmaceuticals and remedies along with days of incapacity to work. Moreover, sociodemographic factors of influence (eg, age, gender and level of education) together with data regarding health-related quality of life will be included in the analysis.

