Interdisciplinary multimodal pain therapy (MPT) describes the simultaneous, comprehensive treatment in which various somatic, physical and psychological interventions are integrated according to a predefined treatment plan with an identified therapeutic goal. The treatment is provided in small groups with a maximum of eight patients by a team of therapists consisting of physicians, psychologists or psychotherapists and other disciplines such as physiotherapists and others.^14^ MPT is currently considered the gold standard in pain management and treatment for patients with chronic or potentially chronic back pain.^15^ The efficacy of interdisciplinary MPT in the treatment of chronic or recurrent back pain with risk of chronification has already been proven in various studies.^8 13 14 16–20^ The term recurrent describes pain episodes that reoccur after a symptom-free period of at least 6 months.^8^ Chronification, moreover, describes the transition from temporary to permanent, or chronic, back pain. After successful MPT, patients usually return to the monodisciplinary treatment of their general practitioner or orthopaedist. As a result, the risk of recurrence remains with the end of MPT. The goal of this new approach to the treatment of back pain is to achieve sustainability of MPT by combining MPT with relapse prophylaxis (RP). Thus, what is learnt during multimodal treatment in terms of physical activity and lifestyle can be applied to everyday life in the long term.

The intervention examined in this study, the 12-month RP programme, immediately follows the 4-week MPT. Like the MPT, the RP will be performed by the Rehabilitation Center, Bad Zwischenahn, on an outpatient basis. The rehabilitation centre is completely independent of the evaluating institution. The RP aims not only to provide prophylaxis against chronifying back pain relapses but also to support life-integrated physical activity. RP is the all-important link between the curative MPT phase beforehand and the patient’s physical activity afterwards. The patient will be assigned to one of three RP paths at the end of the MPT as part of an assessment during the interdisciplinary rounds and team meetings. The paths correspond to RP programmes with three different intensities (low, medium and high) for which the patient will be selected based on the severity of his or her complaints (see figure 1).

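### T2 questionnaires and reminders come from the RP provider in the IG and from the health insurer in the CG, so sender coincides with arm for functional capacity and quality of life

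*Protocol article*

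**What the plan says.** The Measurements section sets the 12-month survey up by arm. The sentence reads "Reminders and the final questionnaires (T2) for the IG will be sent by the Rehabilitation Center, while those for the CG", and it ends by naming the health insurance fund as the sender for the CG. The body that writes to the IG is also the provider of the intervention, as the Introduction states: "Like the MPT, the RP will be performed by the Rehabilitation Center, Bad Zwischenahn, on an outpatient basis".

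The earlier surveys are described by a single route for both arms: "The questionnaire will be handed out directly at the Rehabilitation Center or sent by mail in individual cases for T0", and likewise after the 4-week MPT (T1). Reminders follow the same calendar in both arms, the first after two weeks and then "A second reminder will be sent after an additional 10 days". The T2 form carries the FFbH-R, EQ-5D, VAS and Pain Disability Index, and also satisfaction items: "All questionnaires except for T0 will include questions regarding patient satisfaction and experience with the intervention".

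These data have three uses. H2 (functional capacity) is tested between arms with a two-sided t-test at 0.05 (Secondary outcomes). Health-related quality of life of both arms enters the incremental cost-effectiveness analysis (Health economic analysis). H3 (positive perception by patients) is assessed by paper questionnaire. Missing values in the secondary outcomes are to be imputed by a Markov chain Monte Carlo method. The article gives no reason for the split of senders and does not list it among the limitations.

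**The concern.** In an open trial with patient-reported outcomes, the survey procedure should be the same in both arms, so that a difference in answers can be attributed to treatment. Here it is the same up to T1 and then diverges after allocation, exactly along the line of the comparison.

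The two senders are not interchangeable from the patient's side. An IG patient hears from the institution that has cared for him or her for the past year. A CG patient hears from the fund that receives incapacity certificates, in a trial where entitlement to sick pay is an inclusion criterion. The sender may affect two things: who returns the form, and what those who return it write down. Either could create or hide a difference in FFbH-R or EQ-5D that has nothing to do with RP. At stake are H2 and the quality-of-life side of the cost-effectiveness result.

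**Working it through.** The plan states no figure on this point, so there is none to reproduce. The check is first a reading of the text, then an illustration on assumed inputs.

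**Step 1: overlap.** IG means sender = centre; CG means sender = fund. No exception is described, so no patient has the other combination. A model with terms for both arm and sender cannot be fitted, because the two columns are identical. The estimated T2 contrast is

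observed difference = RP effect + sender effect on answers + effect of differential response,

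and the data do not identify the three parts separately.

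**Step 2: what imputation can do.** It replaces missing answers and leaves given answers as they are, so it cannot touch the second term. It reduces the third only if the variables in the imputation model explain the difference in response.

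**Step 3: which outcomes are exposed.**
- Days of incapacity to work (H1): claims data, not exposed.
- Claims-based costs: not exposed.
- FFbH-R (H2), EQ-5D and VAS: T2 questionnaire, compared between arms, exposed.
- Satisfaction (H3): T2 questionnaire, no between-arm test stated. Here the issue is only that the provider solicits IG patients' opinion of its own programme.

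**Step 4: illustration of differential response (assumed inputs).** The article gives no expected T2 response by arm. If a share p responds and non-responders are δ SD worse, the responder mean overstates the arm mean by (1 − p)·δ. With p = 0.80 in the IG, 0.60 in the CG and δ = 0.3:
- IG: 0.20 × 0.3 = 0.06 SD
- CG: 0.40 × 0.3 = 0.12 SD
- shift in IG − CG: 0.06 − 0.12 = −0.06 SD, that is, *against* the IG.

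A normal selection model, with overstatement ρ·φ(c)/p per arm and c the (1 − p) normal quantile, gives a range for ρ from 0.1 to 0.5:
- 80% vs 70%: 0.015 to 0.073 SD
- 90% vs 60%: 0.045 to 0.224 SD

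Again the shift is against the arm with the higher response, if healthier patients respond more. These values are before any imputation.

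**Step 5: illustration of a reporting shift (assumed inputs).** Take the plan's 147 per group, full response, no clustering and no true effect. The standard error of a standardised difference is √(2/147) = 0.1166. For a spurious shift b, the two-sided rejection rate is Φ(b/0.1166 − 1.96) + Φ(−b/0.1166 − 1.96):

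| b (SD) | rejection rate |
|---|---|
| 0.05 | 7.1% |
| 0.10 | 13.8% |
| 0.15 | 25.1% |
| 0.20 | 40.3% |

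With 80% and 70% response, the same shifts give 6.6%, 11.5%, 19.9% and 31.6%. None of these shifts is an estimate for this trial. They show only that a modest one would matter for a test at 5%.

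**The case against.** Several points on the other side are sound and limit the conclusion.

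- *The primary outcome is untouched.* A reader might infer that the trial's main result is biased, or might scale an assumed sender effect against the planning effect d = 0.34. The text does not support this: that effect size belongs to days of incapacity to work, which come from claims. The article gives no planning effect for FFbH-R or EQ-5D.
- *The direction is open.* It is tempting to say the arrangement favours the IG because patients wish to please the provider. Step 4 shows that better response in the IG could push the other way and partly cancel such an effect.
- *H3 is not a between-arm test.* A reader might infer that the satisfaction comparison is confounded. No such comparison is stated, and the CG receives no RP to rate.
- *Sender is not recipient.* The article does not say to whom forms are returned or that the fund sees any answers. It describes pseudonymised data accessible only to project members. That CG patients report disability to their payer is therefore conjecture; how patients perceive the request is the most that can be argued.
- *A common sender is a partial cure.* Patients know their arm, and the RP includes a session at the centre at one year, so some wish to please the provider would persist.

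None of this removes the central fact: sender and arm coincide by design, without a stated reason. An analysis plan that is not shown could not undo it. The sentence on reminders can also be read to include those for T1, which falls after the centre learns the allocation in the third week of MPT. On that reading the split starts slightly earlier.

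**Conclusion.** The point holds as an avoidable weakness in the data collection for secondary outcomes. The text establishes that the T2 sender is fully aligned with arm. It follows that response and self-report on FFbH-R (H2) and EQ-5D/VAS *may* differ between arms for reasons other than RP, and that no analysis can tell the two apart. It does not follow that a bias is present, that it is large, or that it favours either arm. Size and direction cannot be derived from the document, and the figures above rest wholly on assumed response rates, correlations and shifts. H1 and claims-based costs are unaffected. For H3, the only concern is that the provider itself solicits IG satisfaction. A cheap improvement is available and should be made, or the split should be disclosed.

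**What to change.** Send the T2 questionnaire and all reminders to both arms from one and the same body, with an identical cover letter, identical timing and return to the evaluator, which the Introduction describes as independent of the centre. All patients are members of the fund and all attend the centre for MPT, so either body should be able to reach everyone. Report T2 response by arm.

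The cost is that one body handles about 150 more questionnaires (147 per group in the plan) plus up to two reminders each, at most 3 × 147 = 441 items. No new measurement is needed. Bias from patients knowing their arm remains.

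The article sets deletion ten years after the end of the study, by 31 March 2033 at the latest, which suggests that T2 mailing may already be complete. In that case, report response by arm, add a missing-not-at-random sensitivity analysis for FFbH-R and EQ-5D/VAS, and state the split of senders as a limitation for H2, the quality-of-life results and IG satisfaction.

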### Study population

The study population will comprise members of the regional health insurance fund AOK Lower Saxony, residing in the northwest of Lower Saxony (see online supplemental figure S1). The specific inclusion and exclusion criteria are shown in table 2.

10.1136/bmjopen-2022-067412.supp1Supplementary data

**Table 2 T2:** Inclusion and exclusion criteria

Inclusion criteria	
Membership	AOK Lower Saxony
Region	Northwest of Lower Saxony (see online supplemental figure S1)
Sick pay	Entitled
Incapacity to work	At least 21 days during the last 6 months
Diagnoses	Back pain (ICD: M40–M54, excluding M45, M46 and M49)
Exclusion criteria	
Age	≥62 years
Diagnoses	Mental and behavioural disorders (ICD: F00–F99; 6 months before) Malignant neoplasms (ICD: C00–C97; 12 months before incapacity to work) Injuries (ICD: S00–S99; 6 months before incapacity to work) Chronic back pain (duration of the incapacity to work within the last 6 months is cumulatively longer than 12 weeks)

### Participant recruitment

Each month, with the exception of December, two MPT courses with eight participants each can be held at the Rehabilitation Center, Bad Zwischenahn. In December, a single course will be held. Over a recruitment period of 24 months, a maximum of 368 individuals could begin an MPT. Potentially eligible individuals will be identified and contacted through health insurance employees. If they are interested, they will be informed and invited to participate in the programme. A diagnostic day will then be arranged at the Rehabilitation Center (see online supplemental figure S1), where the medical criteria will be reviewed once again.

The risk factors of a possibly low willingness to participate or a high dropout rate of patients were counteracted in advance by the close involvement of the specialised employees of the AOK. For example, the inclusion and exclusion criteria were developed based on their experience. Nevertheless, the development of the case number and the dropout rate will be subject to constant monitoring so that actions can be taken and incentives implemented if necessary.

### Sample size calculation

The case number calculation was carried out for the primary outcome days of incapacity to work. Currently, the described patient group of AOK-insured persons has an average number of 37 days off work (SD: 58) per year. It is assumed that the average number of 37 days off work per year will decrease in the IG by 40% (or 15 days) compared with the CG. This results in an effect size of d=0.3409275. To test with a power of 80% (1−ß=0.8) and a significance level of 5% (ɑ error=0.05), a case number of 137 subjects per group is required for significant proof of the expected effect. The number of cases was calculated using the software G*Power (see online supplemental figureS2).

Taking an intraclass correlation coefficient of 0.01 and a design effect of 1.1 at an average cluster size of 15.3 (22×16+2×8) into account, the required number of cases is 293 subjects, that is, 147 subjects per group.^29–32^ Considering a drop-out of 10% for patients who drop out during the MPT, that is, before randomisation, results in a required total case number of 322. The available population covers the required case number (see figure 3 and online supplemental figure S2).

10.1136/bmjopen-2022-067412.supp2Supplementary data

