#### Primary outcome

The data will be analysed by reference to the primary outcome (days of incapacity to work), which is carried out by intention-to-treat analysis. Patients are analysed according to their original group assignment.

To test the primary hypothesis H_1_ ‘The intervention reduces the number of days of incapacity to work’, an analysis of covariances with cluster adjustment will be performed, using a significance level of 0.05. Covariables included into the model will be age, gender and comorbidities (eg, depression). In addition, a hypothesis test (two-sided t-test with a significance level of 0.05) will be performed.

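### The effect size of 0.341 does not follow from the stated 15-day difference and SD of 58, which give 0.259; with SD 58 in both arms, power at 137 per group is about 57%, not 80%

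*Protocol article*

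**What the plan says.** Protocol article, Sample size calculation. The inputs for the primary outcome are in two sentences. The first reads "Currently, the described patient group of AOK-insured persons has an average number of 37 days off work (SD: 58) per year". The second assumes that this number "will decrease in the IG by 40% (or 15 days) compared with the CG". The article then states "This results in an effect size of d=0.3409275" and, for 80% power at the 5% level, derives 137 per group. An intraclass correlation of 0.01 and a design effect of 1.1 at an average cluster size of 15.3 bring this to 293 (147 per group), and 10% drop-out before randomisation brings it to 322. The section concludes: "The available population covers the required case number", with reference to figure 3 and supplemental figure S2.

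The section does not say whether the test is one- or two-sided. The Primary outcome section does: "two-sided t-test with a significance level of 0.05". Participant recruitment caps the number who can begin the multimodal therapy at 368 over 24 months.

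**The concern.** The wording presents d as the result of the figures just before it. Only one SD appears anywhere in the article. Dividing the stated difference by that SD gives a clearly smaller effect size, and 137, 147, 293 and 322 all rest on the larger one.

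Two things are at stake. One is the 80% power claimed for the primary outcome, which determines how much a non-significant result can tell us. The other is the statement that capacity is sufficient. Participant recruitment says that case numbers will be monitored so that action can be taken, and monitoring against 322 reassures only if 322 is the right target.

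**Working it through.** **Inputs.** Sample size calculation: mean 37, SD 58, difference 15 (40% of 37 = 14.8), power 80%, alpha 5%, ICC 0.01, cluster size 15.3, design effect 1.1, drop-out 10%. Primary outcome: two-sided test. Participant recruitment: at most 368 starters.

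**1. The plan's own figure, from d to n.** A two-sample t-test with d = 0.3409275, two-sided 5% and 80% power needs 136.02, so 137 per group. This reproduces. A one-sided test would give 108. The step from d to n is therefore sound and two-sided.

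**2. From the stated inputs to d.** d = difference/SD = 15/58 = 0.259, or 14.8/58 = 0.255. Neither gives 0.341.

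**3. What the stated d would need.**
- Common SD: 15/0.3409275 = 44.0.
- With 58 in the control group and d = difference/√((s₁² + s₂²)/2), the intervention-group SD is √(2 × 44.0² − 58²) ≈ 22.5. That is a 61% fall in SD (1 − 22.5/58) beside a 40% fall in the mean.
- If the SD fell in proportion to the mean (0.6 × 58 = 34.8), the common SD would be 47.8 and d = 15/47.8 = 0.314.

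**4. Consequence if SD is 58 in both arms.**
- Power at 137 per group: 56.9%.
- Needed for 80% power: 235.7, so 236 per group, 472 in total.
- With the stated design effect: 472 × 1.1 = 519.2, about 520. With 10% drop-out: 519.2/0.9 = 576.9, about 577 starters.
- The stated ICC and cluster size give 1 + (15.3 − 1) × 0.01 = 1.143 rather than 1.1. Then 472 × 1.143 = 539.5, about 540, and 539.5/0.9 = 599.4, about 600 starters.
- The 472 exceeds 368 even before clustering and drop-out.

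**5. Power at planned and maximum size (SD 58 in both arms).** Randomised: 322 × 0.9 = 290 and 368 × 0.9 = 331. The ranges cover design effects of 1.143 and 1.1.

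| Starters | Randomised | Effective n per group | Power | Detectable at 80% power |
|---|---|---|---|---|
| 322 | 290 | 127–132 | 54–55% | about 20–20.5 days |
| 368 | 331 | 145–150 | 59–61% | about 19 days |

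**6. Dependence on the intervention-group SD** (control SD 58, difference 15; same two design effects).

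| Intervention-group SD | d | n per group | Starters needed | Within 368? | Power at 290 randomised |
|---|---|---|---|---|---|
| 22.5 | 0.341 | 137 | 335–348 | yes | 77–79% |
| 34.8 | 0.314 | 161 | 394–409 | no | 70–72% |
| 58 | 0.259 | 236 | 577–600 | no | 54–55% |

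Starters are 2n × design effect/0.9; for example, 322 × 1.1/0.9 = 393.6 in the second row.

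**The case against.** The strongest reply is that G*Power accepts a separate SD for each group. The article attaches 58 to the patient group as it is now and gives no SD for the intervention group. Supplemental figure S2, which holds the G*Power calculation, is not available here. A second SD of about 22.5 would give the printed d, and the required number would then fit within 368. This stands as a limit on the conclusion: the text cannot distinguish a slip from an unreported input. A reader might infer that the trial is shown to have only 57% power, or that its capacity is shown to be too small. The documents do not support either as an unconditional statement. They also do not rescue the sentence as printed, because it attributes d to figures that do not produce it, and no reason is given for so large a fall in SD.

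Two other defences fail. Covariate adjustment could raise the effective d, but that needs a correlation of √(1 − (0.2586/0.3409)²) ≈ 0.65 with the outcome. The sample size section claims no such gain, and the covariates named are age, gender and comorbidities. A one-sided test does not reproduce 137, contradicts the Primary outcome section, and would still need 186 per group, or 372, before clustering.

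Nor can this be left to a fuller plan. The point is a stated derivation that does not follow, not an omitted detail.

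**Conclusion.** The concern holds in this form: the stated inputs give d = 0.259 (0.255 with 14.8 days), not 0.341, and no SD that would give 0.341 is stated or justified. This part needs no assumption.

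The power and size figures are conditional. With SD 58 in both arms and a two-sided t-test at 5%, power at 137 per group is about 57%, and 80% power needs about 577 starters at the stated design effect (about 600 at 1.143), against 368. Under a proportional fall in SD the shortfall is smaller, but capacity is still exceeded. Only at an intervention-group SD near 22.5 does the coverage statement survive, and even there power at 290 randomised is 77–79%. The error lies in d alone, since the step from d to 137 is correct. How readers would treat a null result is a matter of judgement that the documents do not settle.

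**What to change.** 1. State both SDs entered in G*Power and give the source of any SD other than 58.
2. If no second SD is justified, replace d with 0.259. Restate power with clustering as about 54–55% at 322 starters and 59–61% at 368. Give the difference detectable at 80% power, about 20–20.5 days and about 19 days respectively. Remove the sentence that the available population covers the required number.
3. If a smaller intervention-group SD was intended, say so and report power for SDs of 22.5, 34.8 and 58, as in the second table. Keep the coverage sentence only if the confirmed SD supports it.
4. State which design effect is used, since 1.1 and the 1.143 implied by the stated ICC and cluster size give different totals.

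This rewords one section. No extra enrolment or design change is asked for. The cost is a less favourable stated power.

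### The cluster-inflated total of 293 does not follow from the stated ICC, design effect and cluster size, and drop-out is multiplied in rather than divided out, so 322 starters give about 77–78% power, not 80%

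*Protocol article*

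**What the plan says.** All of the figures are in the protocol article, mostly under Sample size calculation. "The case number calculation was carried out for the primary outcome days of incapacity to work". The effect size is given as d = 0.3409275. With 80% power and a 5% significance level, this leads to 137 patients per group, 274 in total.

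The cluster step reads: "Taking an intraclass correlation coefficient of 0.01 and a design effect of 1.1 at an average cluster size of 15.3". The bracket after it gives the composition as 22 × 16 + 2 × 8. The result is that "the required number of cases is 293 subjects, that is, 147 subjects per group". A 10% loss during MPT, placed before randomisation, then "results in a required total case number of 322".

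The unit of randomisation is set under Study design: "Patients who start an MPT simultaneously in the Rehabilitation Center each form a cluster", with allocation made monthly. Under Participant recruitment, two courses of eight run each month except December, which has one, and the ceiling is 368 starters over 24 months. A cluster is therefore normally 16 patients, and 8 in December.

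**The concern.** The article prints every input to the inflation (ICC, cluster size, design effect, drop-out rate) together with the results, so the chain can be checked without the supplement. It does not reproduce. The total of 293 is lower than either the printed design effect or the printed ICC and cluster size would give, and the drop-out step errs in the same direction.

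The stake is the recruitment target for the primary outcome. The article promises continuous monitoring of case numbers and drop-out, and that monitoring needs a correct target. If 322 is used, the trial could reach it and still fall short of the 80% power it claims, even with every other assumption granted.

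**Working it through.** **Inputs** (Sample size calculation unless noted): d = 0.3409275; power 80%; alpha 0.05; ICC 0.01; mean cluster size 15.3; printed design effect 1.1; drop-out 10% before randomisation; ceiling 368 (Participant recruitment). The test is taken as two-sided, as stated for the primary-outcome t-test.

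**1. Base number: reproduces.** A two-sample t-test at these inputs needs 136.02 per group, so 137, or 274 in total. This matches the article.

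**2. Mean cluster size: reproduces.** (22 × 16 + 2 × 8) / 24 = 368 / 24 = 15.33.

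**3. Cluster step: does not reproduce.** The design effect is DE = 1 + (m − 1) × ICC.

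| Reading | DE | 274 × DE | Total |
|---|---|---|---|
| Printed design effect | 1.1 | 301.4 | 302 |
| ICC 0.01, m = 15.3 | 1.143 | 313.2 | 314 |
| m reduced by 10% loss (15.3 × 0.9 = 13.8) | 1.128 | 309.0 | 310 (even total) |
| m = required N / 24 | 1.118 | 306.2 | 307 |
| Article | – | – | 293 |

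The fourth row solves N = 274 × [1 + (N/24 − 1) × 0.01], that is N = 274 × 0.99 / (1 − 274/2400) = 306.2.

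The inflation actually applied is 293 / 274 = 1.069. Since 274 × 1.07 = 293.2, it would fit a cluster of 8 (1 + 7 × 0.01 = 1.07).

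**4. Drop-out step.** 293 × 1.1 = 322.3, the printed 322. But 322 × 0.9 = 289.8, about 290, which is below the 293 just declared necessary. Division gives 293 / 0.9 = 325.6, so 326.

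**5. Chain redone at the stated d.**
- m = 15.3: 314 randomised (157 per group); 314 / 0.9 = 348.9, so 349 starters, 27 more than 322 and 95% of 368.
- m = N/24: about 307 randomised; 306.2 / 0.9 = 340.2, so about 341 starters, 19 more than 322.

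**6. Power of 322 starters (290 randomised) at d = 0.3409.** The effective number per group is 290 / (2 × DE).

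| DE | Patient-level t-test | t-test on 22 df (24 clusters − 2) |
|---|---|---|
| 1.143 (m = 15.3) | 77.2% | 73.7% |
| 1.111 (m = 290/24 = 12.1) | 78.3% | 74.9% |

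Even at the printed 1.1, the patient-level figure is 78.7%.

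**The case against.** Several points on the other side stand.

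- **The design effect of 1.1 is not itself an error.** It is 1.143 to one decimal, so 1.1 and 15.3 agree. The figure out of line is 293.
- **A cluster of 8 is tempting but not established.** A reader might infer that the size of one course was used by mistake. The article does not say so, and the match is not unique: a base of 133 per group with the printed 1.1 gives 266 × 1.1 = 292.6, also 293 when rounded up. The supplementary figure on the calculation is not at hand. The cause cannot be identified; what can be said is that 1.07 does not fit the monthly unit of randomisation.
- **15.3 is the cluster size at full capacity, before drop-out.** Because the loss comes before randomisation, the randomised clusters are smaller. The 349 starters and 77.2% are therefore the severe end; about 341 and 78.3% are the self-consistent versions.
- **The 22-df power is conditional.** The primary analysis is an analysis of covariance with cluster adjustment plus a t-test; the article does not fix a cluster-level test. That correction would also lower the power of a correctly inflated sample (77.0% at 314), so it should not be counted as the cost of this error.
- **The drop-out slip alone is small:** 322 against 326.

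It can also be said that the loss is modest, that nothing caps recruitment at 322, and that the effect size is a larger problem. The first two limit the consequence but do not make the printed target or power right. The third does not cancel the point, because the multipliers must be correct for any base number.

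**Conclusion.** The point holds. The total of 293 does not follow from 274 under the printed design effect (302) or under the printed ICC and cluster size (314), and 322 does not preserve 293 after a 10% loss. At the stated d, the target is about 19 to 27 starters too low, and its power is about 77–78% rather than 80%; about 74–75% if the test is made on 22 cluster degrees of freedom.

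This rests on an ICC of 0.01, 24 monthly clusters, two-sided alpha of 0.05 and d = 0.3409. The last is doubtful on the article's own figures: "an average number of 37 days off work (SD: 58) per year" and a 15-day difference give 15 / 58 = 0.26, not 0.34, which would need 236 per group before any inflation. The totals here are therefore conditional on d and do not endorse it.

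The loss of power is moderate, but the stated sample size and power are wrong as written.

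**What to change.** In the sample size paragraph, show the design effect unrounded, use the monthly cluster (16, or 8 in December) throughout, and divide by 0.9 for drop-out. At the stated d, print one of:

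- design effect 1.143, 314 randomised (157 per group), 349 starters, with the full-capacity mean of 15.3; or
- about 307 randomised and 341 starters, with the cluster size defined as the required number over 24 clusters.

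Alternatively, keep 322 and state its power at d = 0.3409 as about 77–78%, adding the lower figure of 74–75% if the analysis will use cluster degrees of freedom.

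If d is revised, apply the same two steps to the new base number and do not carry over the 1.07 implied by 293.

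The cost is one reworded paragraph. At the stated d, both corrected targets fit within the 368 maximum, though 349 leaves only 19 places spare. Restating the power costs nothing.
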